#### 2.2.1. Study Outcome Variables (Outcomes)

The following variables will be assessed at pre- and post-intervention (week 0 and week 17, unless otherwise stated) to determine the efficacy and applicability of the IST, as distinguished from the eligibility measures (Section 2.1.1):A.Primary Outcome Variables (Assessment of reversal of dynapenia and sarcopenia):
1.Change in MVIC Knee Extensors:○Specific measurement variable: MVIC of the knee extensors, measured in Newtons (N) with the CIEX SYSTEM machine.○Analysis metric: Absolute change (MVIC_week17_–MVIC_week0_)○Method of aggregation: Mean and Standard Deviation (SD) of the change. The percentage change will also be calculated.○Time point(s): Baseline (week 0) and post-intervention (week 17) assessments.○Clinical Relevance: Knee extensor strength is key to functionality and independence in older adults; its improvement indicates reversal of dynapenia.2.Change at ASMMI:○Specific measurement variable: ASMMI (ASMM in kg/height^2^ in m^2^), measured by bioimpedance (InBody 230).○Analysis metric: Absolute change (ASMMI_week17_–ASMMI_week0_)○Method of aggregation: Mean and SD of change.○Time point(s): Baseline (week 0) and post-intervention (week 17) assessments.○Clinical Relevance: Fundamental diagnostic criterion for sarcopenia (EWGSOP2); an increase indicates improvement in the amount of muscle, essential for metabolic health and reduced frailty.
B.Secondary Outcome Variables

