
* Relevance (common to the previous 4): To evaluate the feasibility, safety, acceptability and perceived difficulty of the IST protocol from the participants’ perspective.

4.Static Posture Parameters:○Specific measurement variable: Key angular and alignment parameters of static posture (e.g., craniovertebral angle, shoulder symmetry, pelvic tilt), assessed from photographs using Kinovea^®^ software. Analysis metric: Absolute change from baseline to week 17, measured in degrees or centimetres. Method of aggregation: Mean and SD of the change for each parameter. Time point(s): Baseline (week 0) and post-intervention (week 17). Clinical relevance: Improvements in postural alignment may be associated with reduced musculoskeletal pain and better overall physical function.5.Physiological Variables at Rest:○Specific measurement variable: Resting systolic blood pressure (SBP) and diastolic blood pressure (DBP) in mmHg, heart rate (HR) in bpm, and peripheral oxygen saturation (SpO2) in %. Analysis metric: Absolute change from baseline to week 17. Method of aggregation: Mean and SD of the changes for each variable. Time point(s): Baseline (week 0) and post-intervention (week 17). Clinical relevance: These variables are monitored primarily for participant safety. Additionally, based on evidence that isometric training may positively influence resting blood pressure (BP) over the medium term [79,80], changes in SBP and DBP will be analysed as a secondary outcome of clinical interest.

C.Exploratory Outcome Variables

Genetic Association: Analysis of the association between selected genetic polymorphisms and the magnitude of the IST response in primary and secondary outcomes. This will be explored using regression models or genotype group comparisons.Other Descriptive Variables: Baseline data from the CGA and laboratory analyses will be used to characterise the sample and to explore other potential factors associated with the training response.

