#### 2.2.2. Pre-Intervention Assessment

One week before starting the 16-week IST, a comprehensive baseline assessment will be performed on the selected subjects to collect baseline data. This assessment, conducted by a physical activity professional and the research group doctor, will allow for detailed monitoring and accurate assessment of the effects of the programme, including the following variables:Physiological Variables: BP and heart rate HR (Omron M3 Comfort^®^ blood pressure monitor, HEM-7134-E, Omron Healthcare Co., Kyoto, Japan) and O2 saturation (OXYM4000 pulse oximeter, Quirumed S.L.U., Valencia, Spain) will be measured. Three resting measurements will be taken per participant, using the mean as the final data.Functional Capacity:○MVIC: The MVIC of each muscle group of the IST programme will be assessed at individualised intermediate angles (determined according to anatomical structure and motor restrictions, recorded with a HALO© digital goniometer). The CIEX SYSTEM machine (Ciex Systems©, Durango, Spain) with sensors and Chronojump software (Chronojump Boscosystems^®^, Barcelona, Spain) will be used for instantaneous measurement and visualisation of strength, tools also used in all IST sessions and for monitoring purposes.○Static Posture Assessment: Participants will be photographed in anatomical position (frontal and sagittal planes) with a Casio Exilim Pro EX-F1 camera (configuration: level tripod, lens at umbilical height, at 4 m, optical zoom, aperture priority, focal length 50 mm, f5.6, ISO 200) [81]. An analysis of documented validity and reliability for postural analysis will be performed with Kinovea^®^ software (v.0.9.x+) [82,83]. Adhesive markers or direct image identification may be used for key anatomical points [84] (sagittal: tragus, C7, acromion, greater trochanter, lateral femoral epicondyle, peroneal malleolus; frontal: acromions, anterior superior iliac spine (ASIS), posterior superior iliac spine (PSIS), patellar centre, tibial malleoli). Postural parameters will be calculated from these points (sagittal: head-neck alignment (HNA) [82], shoulder alignment, estimated spinal curvatures, pelvic tilt [84], knee alignment; frontal: head tilt/symmetry, shoulder height, pelvic symmetry [81], lower limb alignment [82]). Angles (degrees) and distances (cm/mm, after calibration if size reference is used) shall be recorded. Pre-post change will be an outcome of interest. Image analysis shall be performed, if possible, by a blinded assessor (see Section 2.1.3) [83].HRQoL: The EuroQol EQ-5D-5L questionnaire (5 items, 5 dimensions, 5 response levels) will be used [85,86]. This instrument includes two parts: a descriptive system comprising five dimensions (mobility, self-care, usual activities, pain/discomfort, anxiety/depression), each with five response levels, and a VAS where participants rate their overall health.Applicability of the IST Protocol (scales administered post-intervention):○Safety (H1): Assessed by: (1) Analysis of Adverse Events (AEs) (incidence, type, severity, relationship to IST) over 16 weeks (procedures detailed in Section 2.4.3); ‘low risk’ if the incidence of IST injuries is minimal. (2) Perceived Safety: 5-point Likert scale (1 = extremely unsafe, 5 = extremely safe) post-programme, with face validity and based on similar approaches [87]; a mean score ≥ 4 will be expected.○Acceptability (H2): Assessed by compliance rates (≥90% sessions) and overall satisfaction (5-point Likert scale: 1 = extremely dissatisfied, 5 = extremely satisfied) post-programme, using validated measures [88]; a mean satisfaction score ≥ 4 will be expected.○Difficulty (H3): Assessed with a 5-point Likert scale on perceived challenge (1 = not challenging at all, 5 = extremely challenging) post-programme, validated approach [89]; a mean score ≤ 2 will be expected.Genetic Analysis: Saliva samples will be collected using buccal swabs (4N6FLOQSwab, Life Technologies, Waltham, MA, USA). DNA will be extracted from these samples (QIAmp DNA Mini kit, Qiagen, Venlo, The Netherlands) and subsequently quantified (Qubit, Life Technologies). Genetic polymorphisms, specifically Single Nucleotide Polymorphisms (SNPs) and Insertions/Deletions (INDELs), will be analysed in genes associated with the response to strength training, hypertrophy, and strength gains [63,64,65,66,67,68,69,71,72,73]. Specifically, genes linked to the following will be analysed:○Muscle fibre typology: such as ACTN3 (R variant associated with a higher proportion of type II fibres, crucial for strength/power and affected by sarcopenia/dynapenia in ageing) [63,64].○Response to training: including ACE [63,65,66], NRF2, CKMM, MCT1, AMPD1, and the co-activators PPARGC1A and PPARGC1B (involved in mitochondrial biogenesis and exercise adaptation).○Muscle fibre damage and regeneration: genes such as IGF2, MLCK, CASP [72], MMP3 [72], TNC and GDF5 [73], which influence the response to exercise microtrauma and its repair. Moderate exercise-induced muscle damage (EIMD), potentially triggered by IST at long angles, is considered to contribute to remodelling and adaptation.○Vascularisation: NOS3 and VEGFA [67,69], essential for oxygen/nutrient supply, muscle growth and recovery, optimising metabolic stress and hypertrophic response.○Inflammation: TNF-α, CRP [60], IL-6 [60] and IL6-R, which are relevant because inflammation contributes to sarcopenia and modulates the anabolic response [70].○Oxidative damage response capacity: SOD2 [71], CAT and GPX, crucial for muscle recovery and adaptation to training stress.○Fat and carbohydrate metabolism (nutrigenomic factors): Polymorphisms in FABP2, ADRB2, ADRB3, FAT/CD36, UCP2, GCKR, ADCY5 and GIPR, which may influence nutrient uptake and hypertrophic response [74,75,76].

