#### 2.3.2. Analysis Strategy

Primary and secondary quantitative variables will be compared pre-post with Student’s *t*-tests for related samples, after testing for normality (Shapiro-Wilk). If the data are not normally distributed or contain outliers, non-parametric tests (e.g., the Wilcoxon signed-rank test) will be employed. Effect sizes (Cohen’s d) and confidence intervals will be calculated. Multivariate analyses will include a multiple linear regression to explore the influence of genetic and environmental variables on strength and muscle mass improvement, with Bonferroni correction for genetic analyses. Qualitative variables (e.g., sarcopenia diagnosis) will be analysed by using McNemar tests. Applicability variables (Likert scales, adverse events) will be analysed with descriptive statistics and *t*-tests or Wilcoxon tests for pre-post comparisons on Likert scales. Additionally, exploratory subgroup analyses will be performed to assess whether the response to IST on primary variables differs according to sex, age ranges (70–79 vs. ≥80 years) and baseline severity of sarcopenia/dynapenia. Adjustment for baseline covariates will be considered in regression models. The software will be IBM SPSS v29.0 and R v4.3.1.

For the assessment of the secondary hypotheses concerning the applicability (Section 2.2.2) of the IST protocol, specific analyses will be carried out:

Hypothesis H1 (low injury risk): This will be assessed through two approaches. First, Adverse Events (AEs) will be recorded (including their type, severity, and causality), and ‘low risk’ will be inferred if the incidence of IST-related injuries is minimal and comparable to or lower than rates reported in the literature for strength training in older adults [1,33,34,35]. Second, Perceived Safety will be measured post-intervention using a 5-point Likert scale; the approach for this subjective scale is based on similar methods used in previous research [87]. The hypothesis will be supported by a mean score of ≥4.

Hypothesis H2 (high acceptance): This will be assessed by: (1) compliance rate, with a success threshold of ≥90% of completed sessions, and (2) a satisfaction score from a 5-point Likert scale administered post-intervention, using a validated measurement approach [88]. The hypothesis will be supported by a mean satisfaction score of ≥4.

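### One raw-change metric is set for every posture parameter; where the optimum is neutral and deviation can go either way, mean change does not measure improvement in alignment

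*Protocol article*

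**What the plan says.** Section 2.2.1, secondary outcome 4, describes the variable as "Key angular and alignment parameters of static posture (e.g., craniovertebral angle, shoulder symmetry, pelvic tilt), assessed from photographs using Kinovea". The list is given by example. The metric and the aggregation are set together, once for all of them: "Analysis metric: Absolute change from baseline to week 17, measured in degrees or centimetres. Method of aggregation: Mean and SD of the change for each" of them. The stated clinical relevance is improvement in alignment.

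The same section shows what the term means in this protocol. For the primary outcomes it is written as a difference: "Absolute change (MVIC_week17_–MVIC_week0" for knee extensor strength, and "Analysis metric: Absolute change (ASMMI_week17_–ASMMI_week0" for the muscle mass index. It is therefore a signed difference in original units, as opposed to a percentage change.

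Section 2.2.2 (Static Posture Assessment) lists the parameters. The sagittal ones include head-neck alignment, shoulder alignment, spinal curvatures, pelvic tilt and knee alignment. The others are "frontal: head tilt/symmetry, shoulder height, pelvic symmetry [81], lower limb alignment [82". Angles and distances are to be recorded. Neither section gives a sign convention, a neutral value or a direction that counts as better.

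Section 2.3.2 closes the chain: "Primary and secondary quantitative variables will be compared pre-post" with paired t-tests, or a rank test such as the Wilcoxon signed-rank if the data are non-normal or contain outliers.

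**The concern.** Week 17 minus week 0 works for strength, gait speed and muscle mass, where more is better. Posture item 4 carries it over unchanged to parameters for which neither more nor less is better as such.

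Take two people, one with the right shoulder 2 cm high (+2) and one with the left shoulder 2 cm high (-2), and suppose both are fully corrected. Their changes are -2 and +2. Both improved, and the mean change is 0.

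The Wilcoxon fallback does not avoid this. When deviations are balanced and shrink in proportion, the signed changes are symmetric about zero, which is exactly the null hypothesis of the signed-rank test.

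At stake is how a named secondary outcome is read. A null result could be reported as no postural effect when alignment did improve. A non-zero mean could partly reflect which side predominated among 18 people.

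**Working it through.** **The plan's own figure.** Section 2.3.1 uses d = 0.80, 80% power and two-sided alpha 0.05. With the noncentral t distribution (df = n - 1, noncentrality d x sqrt(n)), n = 14 gives 79.0% and n = 15 gives 82.1%, so N = 15. Allowing for 15% losses, 15 / 0.85 = 17.6, rounded up to 18. Both figures reproduce. They rest on quadriceps strength and have no bearing on posture.

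**Inputs for posture.** The documents give no SD, error or effect for any posture parameter, so all of these are assumptions:
- signed deviation from neutral at baseline: normal, SD 3 degrees, group mean m = 0, 1.5, 3 or 6 degrees;
- every participant's true deviation halved at week 17;
- measurement error SD 1 degree at each visit;
- n = 15, the evaluable number in Section 2.3.1.

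**Signed change (the stated metric).** The mean is -0.5 x m. The SD of change is sqrt(0.5² x 3² + 2 x 1²) = sqrt(4.25) = 2.06 degrees. For m = 0 the mean is 0 and the test rejects at its alpha level. For m = 3 the standardised change is 1.5 / 2.06 = 0.73.

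**Change in size of deviation, balanced sides (m = 0).** The mean of |X| for a normal variable centred on zero is 0.798 x SD. The observed SD is sqrt(9 + 1) = 3.16 at baseline and sqrt(2.25 + 1) = 1.80 at week 17. The mean change is 0.798 x (1.80 - 3.16) = -1.08 degrees, which agrees with the simulation.

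**Results** (20,000 simulated trials per row, paired t-test, two-sided 0.05):

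| Group mean deviation | Correction | Signed: mean change | Signed: power | Size: mean change | Size: power |
|---|---|---|---|---|---|
| 0 | 50% | 0.00 | 5% | -1.08 | about 73% |
| 0 | 30% | 0.00 | 5% | -0.66 | 41% |
| 1.5 | 50% | -0.75 | 26% | -1.24 | 81% |
| 3 | 50% | -1.50 | 75% | -1.67 | 94% |
| 6 | 50% | -3.00 | over 99% | -3.00 | over 99% |

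At n = 18 with balanced sides and a 50% correction, the figures are 5% and 83%. With no true change, the test on size of deviation rejects in 5%, so its advantage is not bought with false positives.

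**Coding.** If a parameter is already stored as an unsigned size of asymmetry, week 17 minus week 0 of that value is the size metric, and nothing is lost.

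**The case against.** The strongest reply is that a signed change is not the same as a signed score. Section 2.2.1 shows how the change is formed, not how each visit's value is coded. Shoulder and pelvic symmetry can naturally be recorded as non-negative sizes, and then the stated metric is already the right one. Section 2.1.4 also promises a pre-established data dictionary, and an analysis plan that is not shown may settle the coding.

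Much of this stands. No section assigns a sign to left or right, so for the symmetry items the problem is conditional. It does not dispose of the point. Raw angles such as pelvic tilt, knee or lower limb alignment and head tilt are not sizes of deviation unless someone defines them so. A data dictionary codes variables; it does not alter the metric that Section 2.2.1 has fixed. A later plan that followed that section literally would inherit the problem.

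Three stronger readings are tempting and are not supported:
- A reader might infer that the analysis cannot detect postural improvement however large. That requires both signed values and balanced sides. With a group mean of 6 degrees under the assumptions above, both metrics have over 99% power.
- A reader might infer that mean change will come out near zero. The documents give no distribution of any posture parameter, so the mix of sides is unknown.
- A reader might take the metric as the magnitude of each person's change, so that measurement noise alone would count as effect. The formulas for the primary outcomes show that this is not what the plan means.

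It is also fair that posture is the fourth secondary item in an exploratory single-arm trial, and that none of H1 to H4 concerns it.

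**Conclusion.** The point holds in a limited form. For posture parameters with a neutral optimum and two possible directions of deviation, the mean raw change and its paired test do not measure the improvement in alignment that the outcome is meant to show.

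The loss depends on two things the documents do not state: whether values carry a sign, and how deviations are spread around neutral. Under the assumed SD, error and halving, it runs from near-total with balanced sides (5% against about 73% power), through partial with a group lean of 1.5 or 3 degrees (26% against 81%, 75% against 94%), to none when nearly everyone deviates the same way or unsigned sizes are recorded. Parameters with one direction of improvement, such as craniovertebral angle, are not affected.

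This is a minor correction to a secondary outcome. The primary outcomes, the sample size and the data to be collected are untouched.

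**What to change.** In Section 2.2.1, secondary outcome 4, add that for parameters whose optimum is neutral the score at each visit is |value - neutral|, with the neutral value for each parameter fixed before analysis. The outcome is week 17 minus week 0 of that score, so a negative value means improvement. List the parameters this covers: pelvic tilt, knee and lower limb alignment, head tilt, and shoulder height and pelvic symmetry. Keep the signed change for one-directional parameters such as craniovertebral angle. The paired test in Section 2.3.2 can stay as it is.

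The cost is a short addition to the text and one derived variable per parameter from the same photographs. The direction of deviation is no longer visible in the score and needs a separate descriptive line. If the symmetry items were always meant to be recorded as sizes, the addition simply documents that.

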#### 2.2.2. Pre-Intervention Assessment

One week before starting the 16-week IST, a comprehensive baseline assessment will be performed on the selected subjects to collect baseline data. This assessment, conducted by a physical activity professional and the research group doctor, will allow for detailed monitoring and accurate assessment of the effects of the programme, including the following variables:Physiological Variables: BP and heart rate HR (Omron M3 Comfort^®^ blood pressure monitor, HEM-7134-E, Omron Healthcare Co., Kyoto, Japan) and O2 saturation (OXYM4000 pulse oximeter, Quirumed S.L.U., Valencia, Spain) will be measured. Three resting measurements will be taken per participant, using the mean as the final data.Functional Capacity:○MVIC: The MVIC of each muscle group of the IST programme will be assessed at individualised intermediate angles (determined according to anatomical structure and motor restrictions, recorded with a HALO© digital goniometer). The CIEX SYSTEM machine (Ciex Systems©, Durango, Spain) with sensors and Chronojump software (Chronojump Boscosystems^®^, Barcelona, Spain) will be used for instantaneous measurement and visualisation of strength, tools also used in all IST sessions and for monitoring purposes.○Static Posture Assessment: Participants will be photographed in anatomical position (frontal and sagittal planes) with a Casio Exilim Pro EX-F1 camera (configuration: level tripod, lens at umbilical height, at 4 m, optical zoom, aperture priority, focal length 50 mm, f5.6, ISO 200) [81]. An analysis of documented validity and reliability for postural analysis will be performed with Kinovea^®^ software (v.0.9.x+) [82,83]. Adhesive markers or direct image identification may be used for key anatomical points [84] (sagittal: tragus, C7, acromion, greater trochanter, lateral femoral epicondyle, peroneal malleolus; frontal: acromions, anterior superior iliac spine (ASIS), posterior superior iliac spine (PSIS), patellar centre, tibial malleoli). Postural parameters will be calculated from these points (sagittal: head-neck alignment (HNA) [82], shoulder alignment, estimated spinal curvatures, pelvic tilt [84], knee alignment; frontal: head tilt/symmetry, shoulder height, pelvic symmetry [81], lower limb alignment [82]). Angles (degrees) and distances (cm/mm, after calibration if size reference is used) shall be recorded. Pre-post change will be an outcome of interest. Image analysis shall be performed, if possible, by a blinded assessor (see Section 2.1.3) [83].HRQoL: The EuroQol EQ-5D-5L questionnaire (5 items, 5 dimensions, 5 response levels) will be used [85,86]. This instrument includes two parts: a descriptive system comprising five dimensions (mobility, self-care, usual activities, pain/discomfort, anxiety/depression), each with five response levels, and a VAS where participants rate their overall health.Applicability of the IST Protocol (scales administered post-intervention):○Safety (H1): Assessed by: (1) Analysis of Adverse Events (AEs) (incidence, type, severity, relationship to IST) over 16 weeks (procedures detailed in Section 2.4.3); ‘low risk’ if the incidence of IST injuries is minimal. (2) Perceived Safety: 5-point Likert scale (1 = extremely unsafe, 5 = extremely safe) post-programme, with face validity and based on similar approaches [87]; a mean score ≥ 4 will be expected.○Acceptability (H2): Assessed by compliance rates (≥90% sessions) and overall satisfaction (5-point Likert scale: 1 = extremely dissatisfied, 5 = extremely satisfied) post-programme, using validated measures [88]; a mean satisfaction score ≥ 4 will be expected.○Difficulty (H3): Assessed with a 5-point Likert scale on perceived challenge (1 = not challenging at all, 5 = extremely challenging) post-programme, validated approach [89]; a mean score ≤ 2 will be expected.Genetic Analysis: Saliva samples will be collected using buccal swabs (4N6FLOQSwab, Life Technologies, Waltham, MA, USA). DNA will be extracted from these samples (QIAmp DNA Mini kit, Qiagen, Venlo, The Netherlands) and subsequently quantified (Qubit, Life Technologies). Genetic polymorphisms, specifically Single Nucleotide Polymorphisms (SNPs) and Insertions/Deletions (INDELs), will be analysed in genes associated with the response to strength training, hypertrophy, and strength gains [63,64,65,66,67,68,69,71,72,73]. Specifically, genes linked to the following will be analysed:○Muscle fibre typology: such as ACTN3 (R variant associated with a higher proportion of type II fibres, crucial for strength/power and affected by sarcopenia/dynapenia in ageing) [63,64].○Response to training: including ACE [63,65,66], NRF2, CKMM, MCT1, AMPD1, and the co-activators PPARGC1A and PPARGC1B (involved in mitochondrial biogenesis and exercise adaptation).○Muscle fibre damage and regeneration: genes such as IGF2, MLCK, CASP [72], MMP3 [72], TNC and GDF5 [73], which influence the response to exercise microtrauma and its repair. Moderate exercise-induced muscle damage (EIMD), potentially triggered by IST at long angles, is considered to contribute to remodelling and adaptation.○Vascularisation: NOS3 and VEGFA [67,69], essential for oxygen/nutrient supply, muscle growth and recovery, optimising metabolic stress and hypertrophic response.○Inflammation: TNF-α, CRP [60], IL-6 [60] and IL6-R, which are relevant because inflammation contributes to sarcopenia and modulates the anabolic response [70].○Oxidative damage response capacity: SOD2 [71], CAT and GPX, crucial for muscle recovery and adaptation to training stress.○Fat and carbohydrate metabolism (nutrigenomic factors): Polymorphisms in FABP2, ADRB2, ADRB3, FAT/CD36, UCP2, GCKR, ADCY5 and GIPR, which may influence nutrient uptake and hypertrophic response [74,75,76].

Genetic analysis will be conducted using the Biomark HD system (Standard BioTools, formerly Fluidigm; South San Francisco, CA, USA) in the laboratory facilities of Baigene S.L. (Álava Technology Park, Spain).

